| Study Design                                         | 
The study has three components:
 
 
➤ Open-label, non-randomised dose escalation in 15 individuals aged 18-45 years enrolled through a single centre
 
➤ Randomised dose evaluation in 105 individuals aged 18-45 years enrolled through a single centre. Participants and laboratory staff will be blind to allocation.
 
➤ Open-label, expanded safety evaluation of the highest dose (1 µg) in at least a further 200 individuals aged 18-75 years enrolled through multiple centres
 
 
As part of an amendment to protocol v5.0 a new cohort will be recruited to assess higher dose levels as follows:
 
 
➤ Open-label, non-randomised dose escalation in 12 individuals aged 18-45 years.
 
➤ Non-randomised dose evaluation in 60 individuals aged 18-45 years. Participants and laboratory staff will be blind to allocation.
 
 
In addition participants in the open-label, expanded safety evaluation will be able to delay their second injection until the safety data following the first vaccinations with the higher doses are available. They will be offered the option of the highest dose studied for their second injection, provided this is well tolerated.
 |

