## LAY SUMMARY

COVAC1 is a study that is looking at the use of a new vaccine against the virus (SARS-CoV-2) which causes COVID-19. There are two parts to the study. One part is to assess the safety of this vaccine, since this will be the first time that it has been used in humans. The second part is to see how well, and for how long, the vaccine activates the immune system. It is this activation that may provide protection against developing COVID-19. But this trial is NOT looking at whether or not the vaccine is effective in terms of protection. It is just assessing whether and how well the immune system responds.

Since this is the first time the vaccine has been used in humans, the safety will be assessed initially in healthy young adults. 15 participants aged 18-45 years will be given one of three different doses (0.1, 0.3 and 1 µg) by injection into the muscle, going slowly from the lowest to the highest over a period of several weeks. There will be careful monitoring for any reactions to the vaccine.

As long as there are no safety concerns, the second part of the study can then be started. This will see how well the immune system has been activated using different dose levels of the vaccine. About 100 participants aged 18-45 years will be given one of three doses (0.1, 0.3 and 1 µg). Chance will determine which dose each individual is given. The vaccine is given by injection into the muscle of the upper arm. Two injections, four weeks apart, are needed. There are likely to be mild side-effects near to the injection site. There may also be more general side-effects such as headache, temperature and chills. Participants will be asked to record any symptoms in an online diary. In order to see how well the immune system is responding, participants will need to give blood samples several times during the first 6 weeks; then monthly for a few months; then at 6 months and 12 months. This will happen at one study centre. If this part of the study shows that the vaccines are well tolerated, a new group aged 18-45 will be recruited to study three higher doses (2.5, 5 and 10µg) at one or more centres. If any part of the study shows that a dose is unsafe or poorly tolerated, it will be omitted from further study.

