## 1.5 STUDY DESIGN

This is the first-in-human trial of LNP-nCoVsaRNA vaccine. The first dose escalation and evaluation will be conducted in 18-45 year olds in a single centre supervised by the Chief Investigator and two senior clinicians experienced in first-in-human studies, starting with a sentinel cohort of 15 individuals ([Figure 7](#)) before randomising 105 participants to one of three doses, as described in Section 1.5.1.

Dependent on the safety and immunogenicity data accrued from the first dose escalation cohort of 15, the range of doses studied in a second escalation/evaluation may be extended to include 2.5, 5 and 10 µg dose levels – shown in [Figure 8](#) and described in Section 1.5.2.

The second dose escalation will be conducted in 18-45 year olds in the same centre that conducted the first dose escalation, supervised in the same way. The second dose evaluation will be conducted in the same centre, and also at other centres.

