5. At 48 (-/+5) hours post-vaccination the team will call the three participants vaccinated in Step 4 and go through their diaries. If the reactions are Grade 1-2, or transient Grade 3 that resolve within 24 hours, a sentinel participant may receive 10 µg.
6. At 48 (-/+5) hours post-vaccination the team will call the sentinel participant vaccinated in Step 5 and go through his/her diary. If the reactions are Grade 1-2, or transient Grade 3 that resolve within 24 hours, three further participants may receive 10 µg.
7. At 48 (-/+5) hours post-vaccination the team will call the three participants vaccinated in Step 6 and go through their diaries. When all four participants to receive 10 µg have attended their follow-up visits at Day 7, the safety data accrued to date will be reviewed and, if deemed

acceptable using the same criteria described above, the second dose evaluation cohort of 60 participants may start to be enrolled to receive 2.5, 5 or 10 µg

The steps above describe the fastest dose escalation plan from 2.5–10 µg. However, if there are persistent Grade 3 reactions observed in any of the sentinels, the team will invite the affected participant to attend the study site in order to evaluate these and will proceed to vaccinate a second sentinel at the same dose. The dose will not be escalated until at least 1 participant has provided acceptable safety data to at least 48 (–/+5) hours post-vaccination. If 2 or more of the participants at any dose level in the dose escalation part of the trial have persistent Grade 3 (or worse) reactions, or if 1 or more has a serious adverse reaction, the dose will not be escalated or expanded, and the trial stopping rules described below will be triggered.

**Figure 7. Fastest possible first dose escalation plan, provided there are no persistent Grade 3 (severe), or serious, reactions**

[figure not shown]

 This is the fastest possible dose escalation plan; it is not a fixed schedule. Reasons for a slower dose escalation include persistent Grade 3 or serious reactions, availability of participants and staff, and other operational factors.

**Figure 8. Fastest possible second dose escalation plan, provided there are no persistent Grade 3 (severe), or serious, reactions**

[figure not shown][figure not shown]

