## 9 STATISTICAL CONSIDERATIONS

### 9.1 METHOD OF RANDOMISATION

Only a single site (ICRF) will participate in the first randomised dose-finding study (0.1, 0.3 and 1.0 µg dose levels). Participants will be allocated in a 1:1:1 ratio to the three different doses based on block randomisation.

For the second dose evaluation the doses to be evaluated are 2.5, 5 and 10 µg and this study will be conducted at two or more sites. Participants will be allocated in a 1:1:1 ratio to the three different doses, but this will not be individually randomised. Participants and laboratory staff will not know the dose but the clinic staff will.

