## Immunogenicity

In the first cohort, a total of 105 participants will be included in the randomised dose evaluation of immunogenicity, 35 at each dose. The primary analysis will compare SARS-CoV-2 neutralization IC50 values at 6 weeks (2 weeks after the booster at 4 weeks). Data on mice and recovered COVID-19 patients indicate a standard deviation of approximately 1.5 for neutralization log10 IC50 values. The sample size calculation for the dose evaluation part of this study is based on testing the slope coefficient in a linear regression, using the log10 scale for dose. The study has 97% statistical power (2α=0.05) to detect a true difference of 0.7 (log10 IC50 scale) between adjacent doses (corresponding to a slope of 1.4), 91% power a difference of 0.6, 79% power a difference of 0.5, and 59% power a difference of 0.4.

Data on the first and second cohorts will be considered together to explore the overall relationship between immunogenicity and dose, using the same primary endpoint. As it is suspected that the relationship will be non-linear over this wide dose range (100-fold), evaluation of statistical power is not possible without strong assumptions.

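### The second dose evaluation (Group B2) is allocated 1:1:1 without randomisation, substitute rule or concealment, so site, time and selection can be confounded with dose

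*Protocol*

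**What the plan says.** Protocol 9.1 block-randomises the first dose evaluation (B1: 105 people, 0.1, 0.3 and 1 µg, one site). For the second, "the doses to be evaluated are 2.5, 5 and 10 µg and this study will be conducted at two or more sites", and "Participants will be allocated in a 1:1:1 ratio to the three different doses, but this will not be individually randomised". On knowledge of the dose: "Participants and laboratory staff will not know the dose but the clinic staff will". The Summary of Trial calls B2 non-randomised and names B1 as the only randomised component. Table 1 gives B2 20 people per dose.

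Step 7 of 1.5.2 opens the three doses at one point. After the Day 7 review of the four escalation participants at 10 µg, "the second dose evaluation cohort of 60 participants may start to be enrolled" at any of the three levels.

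The results are used comparatively:
- Section 9.3 plans a safety comparison between 2.5, 5 and 10 µg.
- Section 9.3 also says of immunogenicity: "Data on the first and second cohorts will be considered together to explore the overall relationship between immunogenicity and dose".
- Section 1.4.1 lists comparison of immunogenicity at six dose levels as an objective.
- Sections 1.5.3 and 9.4 have the TSC use the data when recommending the Group C second dose and the dose for efficacy testing.

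**The concern.** A 1:1:1 ratio fixes how many people get each dose. It does not fix who gets it, where or when. As worded, the ratio would be met even if one site or one month held a single dose. The usual reason for non-random allocation in a first-in-human study is that doses must open in sequence. That does not apply here, because step 7 opens all three together. Feasibility is not an obvious bar either, since section 4.1 describes randomising three doses from a paper list at one of the same centres.

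If site, calendar period or participant selection lines up with dose, the within-B2 contrasts in reactogenicity and titre mix those differences with the dose effect. Analysis can repair this only where doses overlap within site and period. The Fisher's exact test named in 9.5 has no site or date term.

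The pooled curve has a separate problem. In Table 1 no dose is common to the first cohort (A1, B1) and the second (A2, B2). The contrast of 0.1–1 µg against 2.5–10 µg is therefore also a contrast of cohort and calendar time.

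**Working it through.** **Inputs.** From 9.3: SD 1.5 for log10 IC50, two-sided 5%, slope test in a linear regression on log10 dose, 35 per dose in B1. From Table 1: 20 per dose in B2. Carrying the SD of 1.5 over to B2 is an assumption.

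**The plan's own figures first.** For B1, x = log10(0.1, 0.3, 1) = −1, −0.523, 0. With 35 per dose, Sxx = 35 × 0.500 = 17.5, so SE(slope) = 1.5/√17.5 = 0.358. The non-central t test on 103 df gives:

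| Adjacent-dose difference (log10) | Slope | Computed power | Stated power |
|---|---|---|---|
| 0.7 | 1.4 | 97.2% | 97% |
| 0.6 | 1.2 | 91.3% | 91% |
| 0.5 | 1.0 | 78.9% | 79% |
| 0.4 | 0.8 | 59.9% | 59% |

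The stated power is reproduced to within 1 point. No power is stated for B2.

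**The same test in B2.** The values log10(2.5, 5, 10) are equally spaced by 0.301.
- Sxx = 20 × 2 × 0.301² = 3.62
- SE(slope) = 1.5/√3.62 = 1.5/1.904 = 0.788

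**Adding a non-dose shift.** Suppose the 2.5 and 10 µg groups differ by s log10 for reasons other than dose, with the 5 µg group halfway between. Then bias in slope = s/log10(10/2.5) = s/0.602. For s = 0.5 the bias is 0.83, or 0.83/0.788 = 1.05 standard errors. If the whole shift sits in the 10 µg group, the bias is the same: 20 × 0.301 × 0.5/3.62 = 0.83. For scale, the slope behind the 97% power figure is 1.4.

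**Error rate of the nominal 5% slope test when dose has no effect** (58 df, linear shift):

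| Assumed shift s (log10) | Error rate |
|---|---|
| 0 (expected under randomisation) | 5% |
| 0.25 | 8.1% |
| 0.50 | 17.9% |
| 0.75 | 34.3% |
| 1.00 | 54.5% |

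The shifts are assumptions; the protocol gives no figure. Randomising leaves the sample size at 3 × 20 = 60.

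**The case against.** The strongest reply is that the design is openly declared. The Summary says non-randomised, 9.3 concedes that the combined-cohort safety comparison is not strictly randomised, and the pooled immunogenicity analysis is exploratory with no power claimed. This stands, and it limits the complaint. But the caveat in 9.3 is attached to the pooled safety comparison, not to the comparison within the second cohort, and disclosure does not remove bias.

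Participants and laboratory staff are blind ("in 60 individuals aged 18-45 years. Participants and laboratory staff will be blind to allocation"). That limits bias in diary reporting and assay reading. It does not prevent confounding by site, time or selection.

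The stakes should not be inflated. In 1.5.3 the planned Group C boost is 10 µg, subject to tolerability, and 1.4.1 judges the efficacy dose in relation to levels in recovered patients, so neither decision rests only on between-dose contrasts in B2.

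A reader might go further than the text allows in four ways:
- **Staff choose each person's dose.** Section 9.1 says that clinic staff know the dose, not that they assign it. A preset or session-wise sequence would fit the wording too. Staff also know the dose in randomised B1 (4.1). What B2 lacks is randomisation or any stated rule.
- **Dose is fully confounded with centre in the pooled curve.** It is not. A1, A2 and B1 are at ICRF, and for B2 "The second dose evaluation will be conducted in the same centre, and also at other centres", so all six doses are given there.
- **Dose is confounded with assay run.** This does not follow from the allocation rule. One central laboratory, blind to dose, runs the assays, and the run layout is not described.
- **The 1 µg prime in Group C can bridge the cohorts.** It cannot identify a cohort effect. B2 has no 1 µg arm. Group C is at collaborating centres, is not screened for SARS-CoV-2 antibodies at entry, and includes only self-selected participants at the Week 4 boost.

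Finally, section 6.8 already refers to cohort B2 when listing samples for early leavers, so randomising may come too late. That is why the fix has a fallback.

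**Conclusion.** The point holds as one of design: no stated figure is wrong. B2 lacks randomisation, a substitute rule and concealment, at two or more sites, with all three doses open at once and no reason given. Its dose comparisons can therefore be biased by site, calendar time or selection.

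The size cannot be known from the protocol. With SD 1.5, an assumed shift of 0.5 log10 aligned with dose gives a bias of about one standard error and an error rate near 18%; shifts of 0.25 to 1.0 span 8% to 55%. Nothing in the document shows that any site or period actually held a single dose.

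The pooled curve has a distinct limitation that randomising B2 would not cure: low versus high dose is confounded with cohort and calendar time, and only partly with centre. The change is worth making because it costs little and leaves the sample size alone.

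**What to change.** **If B2 is still enrolling (9.1).** Randomise 1:1:1 in permuted blocks stratified by site, and release each allocation only after eligibility is confirmed in the electronic data capture system. If one dilution has to serve a whole session, randomise sessions within site and include session in the analysis. Cost: a site-stratified list and amendment wording. Individual randomisation may mean preparing more than one dose level per session.

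**If enrolment is complete.** State how doses were allocated, extend the caveat in 9.3 to the within-B2 comparisons, and adjust those comparisons for site and vaccination date. Tabulate dose by site and by date first, because adjustment helps only where doses overlap. Cost: text and analysis only.

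**Pooled six-dose curve (9.3).** State that low versus high dose is confounded with cohort and calendar time. Add an ICRF-only sensitivity analysis to remove centre differences. It will not remove calendar time, and its precision depends on how many B2 participants ICRF enrolled, which the protocol does not fix.

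**Consistency.** The Lay Summary describes the higher-dose work as "to study three higher doses (2.5, 5 and 10µg) at one or more centres", while 9.1 has two or more sites. Reconcile the two.

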### 9.2 OUTCOME MEASURES

The outcome measures are:

- Solicited local injection site reactions starting within 7 days of administration of the vaccine: pain, tenderness, erythema, swelling
- Solicited systemic reactions starting within 7 days of administration of the vaccine: pyrexia, fatigue, myalgia, headache, chills, arthralgia
- Unsolicited adverse reactions (ARs) throughout the study period (including serious ARs)
- Serious Adverse Events
- Unsolicited adverse events throughout the study period
- The titre of serum neutralising antibodies 2 weeks after the second vaccination in the SARS-CoV-2 pseudovirus-based neutralization assay
- The titre of vaccine-induced serum IgG binding antibody responses to the SARS-CoV-2 S glycoprotein 2 weeks after the first and second vaccinations

The exploratory outcome measures are:

- Cell-mediated vaccine-induced immune responses measured by T- and B- cell ELISpot in participants in the dose escalation and evaluation parts
- Cell-mediated vaccine-induced immune responses measured by flow cytometry and intracellular cytokine staining in participants in the dose escalation and evaluation parts
- The profile of class and sub-class of antibody response
- Laboratory markers of infection and infection-induced immunity

### 9.3 SAMPLE SIZE

#### Safety

In the first cohort, at least 39 (4+35), 39 (4+35), and 242 (42 + 200) participants are expected to receive at least one vaccination at a dose of 0.1 µg, 0.3 µg and 1.0 µg respectively. Safety analyses will include all dose groups but the most robust data will be generated on the 1.0 µg dose.

**Table 8** shows the probability of observing at least 1, 2, 3, or 4 adverse reactions in the 1.0 µg group, by the true frequency. The study is reasonably powered to detect a true frequency of between 1/50 to 1/100 or higher.

**Table 8: Probability (%) of observing X or more adverse reactions by true frequency (First Cohort)**

| Number of notable adverse reactions | True frequency |       |       |       |
|-------------------------------------|----------------|-------|-------|-------|
|                                     | 1/50           | 1/100 | 1/200 | 1/500 |
| 1 or more                           | 99             | 91    | 70    | 38    |
| 2 or more                           | 95             | 69    | 34    | 8     |
| 3 or more                           | 86             | 43    | 12    | 1     |
| 4 or more                           | 71             | 22    | 3     | <1    |

In the second cohort, safety outcomes will be compared between the 2.5, 5, and 10 µg dose groups. In addition: (a) analyses will be conducted of the dose-response relationship across all evaluated doses, combining data across the first and second cohorts, even though this comparison is not strictly randomised (b) the expanded safety cohort will provide additional information on safety although some participants may receive a different dose at their first and second vaccinations.

## Immunogenicity

In the first cohort, a total of 105 participants will be included in the randomised dose evaluation of immunogenicity, 35 at each dose. The primary analysis will compare SARS-CoV-2 neutralization IC50 values at 6 weeks (2 weeks after the booster at 4 weeks). Data on mice and recovered COVID-19 patients indicate a standard deviation of approximately 1.5 for neutralization log10 IC50 values. The sample size calculation for the dose evaluation part of this study is based on testing the slope coefficient in a linear regression, using the log10 scale for dose. The study has 97% statistical power (2α=0.05) to detect a true difference of 0.7 (log10 IC50 scale) between adjacent doses (corresponding to a slope of 1.4), 91% power a difference of 0.6, 79% power a difference of 0.5, and 59% power a difference of 0.4.

Data on the first and second cohorts will be considered together to explore the overall relationship between immunogenicity and dose, using the same primary endpoint. As it is suspected that the relationship will be non-linear over this wide dose range (100-fold), evaluation of statistical power is not possible without strong assumptions.

## 9.4 INTERIM MONITORING & ANALYSES

The trial will be overseen by a Trial Steering Committee (TSC), which will include membership independent of the Trial Management Group (TMG). An Independent Data Monitoring Committee (IDMC) will be set up for the efficacy trial but not for COVAC1. The reason for this is the need for real-time assessment of the safety data. The TSC will be informed by the Chief Investigator when the first participant receives the first injection of 0.1, 0.3 and 1µg, and a report of 7 day reactogenicity will be provided when the first 15 individuals have completed their Week 1 visit. The TSC will receive weekly

progress reports, and will be asked to review the accumulating safety and immunogenicity data in order to recommend which doses(s) should be used to boost the safety expansion cohort, and which dose should be taken forward to efficacy testing. Any adverse reactions that lead to interruption in the schedule for an individual or plan for enrolments described in Section 1.5 will be immediately reported to the TSC. Sites will be requested to notify the Chief Investigator and Project Lead at CTU within 24 hours of any adverse reaction that is a cause for concern as described in [Section 5.1.5](#). These reports will be shared with the Trial Steering Committee immediately. If there are 2 out of 20 participants (10% thereafter) who experience similarly severe adverse reactions, vaccinations will be paused in all individuals and the competent authority informed. The TSC will be asked to review the accumulating safety data from all participants and make a recommendation about resuming vaccinations.

It is anticipated that serological assays will be conducted at two or three time-points during the course of the trial and might lead to changes to the protocol as recommended by the TSC.

## 9.5 ANALYSIS PLAN

A full analysis plan will be provided in a separate Statistical Analysis Plan.

Primary safety analyses will be based on all participants who receive at least one dose of vaccine. Safety endpoints will be compared between the different dose groups. The frequency of adverse events will be tabulated by grade and MedDRA System Organ Class and treatment group, and MedDRA Preferred Term and treatment group. Groups will be compared using Fisher's exact test in terms of the proportion ever experiencing an event in each MedDRA System Organ Class.

Primary analyses of immunological responses at 6 weeks will be based on all participants who receive both the initial vaccination and the booster at 4 weeks. These analyses will exclude participants who are identified as COVID-19 seropositive at baseline (either retrospectively, or those enrolled at the St Mary's Hospital site with known previous SARS-CoV-2 infection). Data will also be censored on participants who acquire SARS-CoV-2 infection (virologically-confirmed) during follow-up or who receive an authorised COVID-19 vaccine.

Immunological responses at all time-points will be compared between the younger and older age groups using cross-sectional analyses and longitudinal multilevel models.

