### 1.5.2 SECOND DOSE ESCALATION AND EVALUATION

Following a review of the cumulative safety data and preliminary immune responses in the first dose escalation cohort on 18th August, the Trial Steering Committee recommended that the trial team evaluate higher doses up to 10 µg. As of 9th August, 120 participants age 18-45 were enrolled to the 3 dose groups, 15 of whom had received their second vaccination. Reactions reported in the first 7 days were absent or mild with the most common local mild reaction being tenderness/discomfort (43%) followed by pain (15%). These appear to increase with dose. The most common mild systemic reactions are fatigue (25%) and headache (23%) with no clear relationship to dose. Moderate reactions have been infrequent: tenderness/discomfort and pain reported by 2% and 1% respectively; fatigue by 3% and headache by 3%. Preliminary immune responses suggested a dose response with earlier responses seen at higher doses, but no more than half the participants in the 0.1 and 0.3 µg groups had seroconverted. Insufficient data were available on the 1 µg group but the overall consensus was that the doses explored to date were too low.

The second dose escalation cohort will proceed through 2.5, 5 and 10 µg as follows over the course of 11 days (minimum):

1. The first participant will receive 2.5 µg and be invited to enter information on local and systemic reactions, into an online diary, that evening and daily thereafter for 6 days.
2. At 48 (-/+5) hours post-vaccination the team will call the first participant and go through his/her diary. If the reactions are Grade 1-2, or transient Grade 3 that resolve within 24 hours, three further participants may receive 2.5 µg
3. At 48 (-/+5) hours post-vaccination the team will call the next three participants and go through their diaries. If the reactions are Grade 1-2, or transient Grade 3 that resolve within 24 hours, a sentinel participant may receive 5 µg.
4. At 48 (-/+5) hours post-vaccination the team will call the sentinel participant at 5 µg vaccinated in Step 3 and go through his/her diary. If the reactions are Grade 1-2, or transient Grade 3 that resolve within 24 hours, three further participants may receive 5 µg.

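### Section 9.5 names only an unordered Fisher's exact test for ordered dose groups, and its ever-had-an-event endpoint gives no dose group to expanded-safety participants who receive two different doses

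*Protocol*

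**What the plan says.** Section 9.5 bases the primary safety analyses on everyone who receives at least one dose and states: "Safety endpoints will be compared between the different dose groups". The only test it names is Fisher's "exact test in terms of the proportion ever experiencing an event in each MedDRA System Organ Class". It does not say whether this is one global test or a set of pairwise tests, and it leaves the full plan to a separate SAP.

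Section 9.3, under Safety, goes further. It pairs a group comparison with the second cohort ("In the second cohort, safety outcomes will be compared between the 2.5, 5, and 10 µg dose groups") and adds that "analyses will be conducted of the dose-response relationship across all evaluated doses, combining data across the first and second cohorts", noting that the pooled comparison is not strictly randomised. It names no method for the dose-response part.

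On group membership, Section 9.3 says that at least "39 (4+35), 39 (4+35), and 242 (42 + 200) participants are expected to receive at least one vaccination" at 0.1, 0.3 and 1.0 µg respectively. The 1.0 µg count thus includes 200 expanded-safety participants. Table 1 and Section 5.1 give those participants 1 µg first and then 1, 2.5, 5 or 10 µg.

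On the expected shape, Section 1.5.2 says of the local reactions: "These appear to increase with dose". It also says that fatigue and headache show no clear relation to dose.

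**The concern.** The p-value of Fisher's test does not change if the dose labels are shuffled. For doses spanning a 100-fold range, it ignores the one thing known about the groups in advance. The immunogenicity analysis in Section 9.3 does use the order, as a slope on log10 dose. Comparing safety across six dose levels is a stated objective, and the three upper doses have 24 people each (4 + 20). If event rates rise steadily, an unordered test will more often fail to show it.

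The second issue is the endpoint. Whether a participant ever had an event belongs to one dose only if both injections were at that dose. A Group C participant given 1 µg and then a higher dose has no single dose group. If the Section 9.3 count is carried into the Section 9.5 comparison, events after the higher boost are counted against 1 µg, which distorts the dose gradient.

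**Working it through.** **Inputs from the protocol.** Groups A and B by dose, Table 1: 39, 39, 42 (first cohort) and 24, 24, 24 (second cohort). Group C: 222 in Table 1, at least 200 in Section 9.3. The two-sided 0.05 level is stated for immunogenicity only and is assumed here for safety. The protocol gives no event rates or power for the Fisher comparison, so all rates below are assumptions.

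**The plan's own figures reproduce.**
- Slope test with 35 per dose, SD 1.5 and scores −1, 0, 1: standard error 1.5/√70 = 0.179. A difference of 0.7 gives noncentrality 3.90 on 103 df and power 97.2%. Differences of 0.6, 0.5 and 0.4 give 91.2, 78.9 and 59.9%. The protocol states 97, 91, 79 and 59%.
- Table 8, first row: 1 − 0.99^242 = 91%, as stated. All cells agree within 1 point at n = 242, so the table does count Group C under 1.0 µg.

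**Test formulas.** With k events among N people, P(x | k) = ΠC(nᵢ, xᵢ)/C(N, k).
- Global Fisher (Freeman-Halton): sum P over tables no more probable than the one observed.
- Exact trend: T = Σ sᵢxᵢ, where sᵢ is the dose score; sum P over tables with T at least as far from its conditional mean.
- Power: total probability, under the assumed rates, of tables with p ≤ 0.05.

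Three-dose results come from full enumeration. Six-dose results come from simulation and carry an error of about 1 to 2 points.

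**Steady rise**

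| Groups | Assumed rates | Fisher | Trend | Gain |
|---|---|---|---|---|
| 39/39/42 | 5, 15, 25% | 62% | 73% | +11 |
| 24/24/24 | 10, 25, 40% | 56% | 63% | +7 |
| Six doses | 5 to 25%, logit-linear in log10 dose | 59% | 79% | +20 |
| Six doses | 10 to 30%, logit-linear | 46% | 69% | +23 |
| Six doses | 10 to 30%, equal steps | 41.8% | 67.0% | +25 |
| Six doses | 2 to 10%, equal steps | 26.1% | 35.0% | +9 |

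Over a wider grid of rates and two-sided definitions, the within-cohort gain runs from about +2 to +12 for 39/39/42 and from +3 to +9 for 24/24/24. Under the null, both tests reject in about 5% of trials or fewer.

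**Other shapes**

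| Groups | Assumed rates | Fisher | Trend | Difference |
|---|---|---|---|---|
| 39/39/42, plateau | 10, 30, 30% | 62.7% | 53.6% | −9 |
| 39/39/42, plateau | 5, 20, 20% | 51.8% | 44.6% | −7 |
| 35/35/35, top dose only | 10, 10, 35% | 75.9% | 73.3% | −3 |
| Six doses, top dose only | 10% in five groups, 40% at 10 µg | 77.8% | 64.4% | −13 |
| 39/39/42, peaked | 10, 40, 10% | 92.2% | 0.7% | −92 |

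The first two rows, the 35/35/35 row and the peaked row use equally spaced scores. Within three doses, the top-dose-only difference is small and its sign depends on the score spacing. Plateau and top-dose-only patterns are monotone, so the trend test's weakness is not confined to non-monotone responses.

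**Group C illustration.** Take the scenario from 10% at 0.1 µg to 30% at 10 µg, as risks over two injections at the same dose.
- 1 µg is the log midpoint. Its logit is (ln(1/9) + ln(3/7))/2 = −1.522, which gives 17.9%.
- With equal, independent risk per injection, the per-injection risk is 1 − √0.821 = 9.4% at 1 µg and 1 − √0.70 = 16.3% at 10 µg.
- For 1 µg then 10 µg: 1 − 0.906 × 0.837 = 24.2%.
- If all 222 are boosted at 10 µg and counted under 1 µg: (42 × 17.9 + 222 × 24.2)/264 = 23.2%.
- If half are: (153 × 17.9 + 111 × 24.2)/264 = 20.6%. If none are: 17.9%.

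**The case against.** The best defence is that the ordered analysis is already planned. Section 9.3 commits to it across all doses, and Section 9.5 defers detail to a SAP that is not shown. This stands. A reader might infer that the trial has no dose-response safety analysis, and the protocol does not support that. What remains is that 9.5 names a test, and the one it names does not match what 9.3 promises.

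Second, the 20 to 25 point gaps require one global Fisher test over six doses, which 9.5 does not specify. Section 9.3 ties group comparison to the second cohort and dose-response to the pooled data. This also stands, and it makes the within-cohort figures the safer guide.

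Third, a reader might infer a fixed power loss, or that Fisher's test should be replaced. Neither follows. The sign reverses for the other shapes shown, and a steady rise is not given for every event. Section 1.5.2 reports no clear dose relation for systemic reactions, and several rat findings in Section 1.1 (raised temperature, weight loss, haemoglobin changes) are reported at 10 µg only.

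Fourth, making a pooled six-dose trend the main test would create a new problem. Dose is nested in cohort, and Section 9.1 says the second cohort is not individually randomised and runs at two or more sites. A cohort difference would appear as a dose trend.

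Fifth, decisions during the trial rest on event rates, confidence intervals and pausing thresholds (Sections 1.4.1, 5.1.5 and 9.4), not on Fisher p-values. The safety analysis is therefore not invalid.

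On Group C, Section 9.3 acknowledges that first and second doses may differ and calls the cohort additional information. It gives no rule for placing such participants in the 9.5 comparison.

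**Conclusion.** The point holds in limited form. Section 9.5 names only an unordered test for ordered doses. Under an assumed steady rise and a global reading of the test, it gives up about 6 to 11 points of power within a cohort in the main scenarios. Across six doses the loss is about 20 to 25 points at moderate rates and nearer 9 at rates of 2 to 10%. It is the better test for plateau and peaked patterns, and for an effect confined to the top of six doses. The two tests complement each other.

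The Group C point does not depend on the choice of test. As written, the endpoint cannot be assigned to one dose for anyone given two different doses. In the illustration, the apparent 1 µg rate moves from 17.9% to as much as 23.2%. The size depends on how many participants are boosted above 1 µg, on the boost dose and on the true rates, none of which the protocol fixes.

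Both are worth correcting. Neither undermines the trial's safety monitoring.

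**What to change.** 1. In Section 9.5, add an exact Cochran-Armitage trend test on log10 dose beside Fisher's test, within each cohort, with both reported. State whether Fisher's test is global or pairwise. Report the pooled six-dose trend as supportive only, and give the reason: dose is nested in cohort and the second cohort is not individually randomised. This supplies the method for the analysis promised in 9.3.

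2. For Group C, tabulate events per vaccination by the dose just received. Keep participants given two different doses out of the comparison of dose groups on ever having an event, so that events after the boost are not attributed to 1 µg.

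The cost is wording in the analysis plan plus a few more tables and tests, with no new data, participants or visits. The trend test has less power under non-linear patterns. Fisher's test stays in place to cover those.
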